## Abstract

**Objectives::**

Non-adherence to tuberculosis (TB) treatment is the leading cause of the increase in drug resistance cases. This study will determine the effectiveness of pharmaceutical-care-based interventions coupled with short messages delivered by a pharmacist on treatment outcomes and adherence among TB patients.

**Methods::**

The study will be conducted in TB Control Center of Pakistan Institute of Medical Sciences Hospital, Islamabad and District Bannu TB Control Center time period will be from August 2019 to September 2021. The patients will be included into the control group (usual care) or the intervention group pharmaceutical care and SMS reminder. The primary outcome includes a change in mean score from baseline in treatment outcomes and adherence, measured by Morisky Medication Adherence Scale, and clinic appointment attendance registration. Secondary outcomes include health-related quality of life of patients, disease knowledge, and patient satisfaction with the intervention.

**Result::**

The major issues in patients with TB are cure rate and medication adherence. The method anticipated in this manuscript could set the foundation of pharmaceutical care and mobile SMS for the future provision of care to improve TB treatment outcomes.

**Conclusion::**

The study will make available fundamental information about the influence of the patient centered program on the adherence and clinical outcomes of patients with TB.

***Trial status and registration:*** Clinical Trials.gov assigned Identifier NCT04645836.

## INTRODUCTION

Tuberculosis (TB) is a leading public health issue globally, and nearly ten million people suffered from TB in 2019, as reported by the World Health Organization (WHO). All over the world, 30 high burden countries are responsible for 87% of all new TB cases each year. Pakistan was ranked fifth in 2019 due to the considerable number (562000 cases) of TB with 15000 cases of drug-resistant TB each year.^1^ This increase in the emergence of drug-resistance TB cases is possibly due to nonadherence, poor follow-up, lack of social and motivational support during the treatment.^2^ Non-adherence to TB treatment remains an essential factor for increasing drug-resistant TB cases in developing countries, including Pakistan.^3^ According to Akhtar et al., drug-resistant TB case is more prevalent in Pakistan in the reproductive age group (57%) and in urban areas (97%).^4^ Directly observed treatment support DOTS strategy has been established to resolve all problems that could arise during treatment. Still, this strategy has numerous barriers to optimal implementation, especially in developing countries, including poor economic conditions, large population density, long travel distances, fragile healthcare system, and shortage of human resources.^3^

Available literature suggests that there has been a constant increase in electronic gadgets throughout the world, including developing countries. Along with mobile equipment technologies, another pharmaceutical care-led strategy is the provision of instructions to patients on illness, medication use, and medication-related issues by a pharmacist.^5^-^7^ Pharmacists play a fundamental part in the management of patients chronic disease through pharmaceutical care. During the administration of pharmaceutical care treatment, the responsible pharmacist provides a cell phone number to patients and encourages them to call if they need any disease management advice.^8^ Recently, the most effective means of communication between patients and healthcare providers have been mobile phone messages, which are very economical and useful in both urban and rural areas.^9^,^10^ Therefore, in Pakistan, the TB control programme immediately needs a suitable and affordable course of action to improve treatment adherence. The current study was designed to determine the effectiveness of a pharmaceutical-care-based intervention coupled with short messages delivered by a pharmacist on treatment outcomes and adherence among TB patients.

## METHODS

### Trial Design:

This trial is a single-blind, randomized parallel study among all eligible new TB patients who are registered and receiving their treatment from the TB Control Center of the Pakistan Institute of Medical Sciences Hospital (PIMS) and District Bannu TB control program (DBTC). The time period will be from August 2019 to September 2021. The study will be randomized into two parallel groups (ratio 1:1): an intervention group (in which patients will be given pharmaceutical care and SMS reminders) versus a control group or a usual care group where participants will receive the same routine standard treatment care as the intervention group, but no pharmaceutical care and SMS text messages will be made (Fig.1).^11^

**Fig.1 F1:**
[figure not shown]
Study flow diagram.

### Primary Objective:

The primary objective of this study is to assess the effectiveness of pharmaceutical care coupled with short messages provided by the pharmacist on treatment outcomes and adherence in newly diagnosed TB patients.

### Secondary Objectives:

Determine whether the patient’s quality of life,score increases in intervention arm patients from baseline to successful completion of treatment. In the intervention arm patient satisfaction feedback response will be assessed.

### Treatment Outcomes:

According to WHO guidelines^12^, treatment outcomes are classified as successful when the TB patient finalizes the treatment medication with an indication of cure and complete. The unsuccessful treatment outcomes are categorized into treatment failure, treatment defaulters, transfer out, or those registered patients whose outcomes are not known after completing the course.

### Inclusion criteria:

Men and women with age >= 18 years,Newly bacteriological confirmed TB cases (less than a month since diagnosis). This restriction (not more than one-month treatment) does not refer to patients whose most recent treatment outcome was a failure and assigned to a new treatment regimen.Have a mobile phone and can receive SMS messages or phone callsAn address or residence location is readily accessible for visiting and willingness to inform the study team of any change of address during the treatment and follow-up period for at least 9 months.Willingness to comply with study procedures and provide written informed consent before study enrollment.

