### Intervention Group:

The study will be conducted among all eligible new TB patients who are registered and receiving their treatment from the TB Control Center of PIMS and DBTC. In the intervention group, the participant’s pharmacist will provide pharmaceutical care education at each follow-up visit and SMS reminders will be sent to patients in local and in national language. The messages will be aimed ‘to take their prescribed anti-TB drugs daily and record the behaviour change during the therapy.

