### Phases of pharmacist counselling:

After documentation of base-line data, patient care interventions will be implemented. Pharmaceutical care will be provided face to face during monthly follow ups visits to health care center. Interventions will be divided into non-pharmacological and pharmacological. Non-pharmacological interventions included guidance on the proper use of drugs and their risks and pharmacological interventions included suspension, addition, or change in medication. If pharmacological interventions seem to be necessary, a collaborative decision will be made by the pharmacist, physician, and patient. The pharmacist will talk over the patient-related barriers to adherence, incomplete information related to medication and disease, and other drug-related problems.The pharmaceutical care and face-to-face counselling to the TB patients will be provided during the first interview, within two weeks of initiating of anti-tuberculosis treatment. The second interview will be conducted within two months. The third interview will be at the six month of the treatment and the final data will be collected before the final sputum test.

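### The inclusion criteria waive the one-month entry limit for patients whose last treatment failed, although the design and primary objective are for new TB patients; the limit also runs on two clocks and does not fit the first counselling window.

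*Protocol article*

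**What the plan says.** Three sections of the protocol article fix the population. Trial Design describes a "randomized parallel study among all eligible new TB patients". Intervention Group repeats this: "The study will be conducted among all eligible new TB patients who are registered". Primary Objective concerns "treatment outcomes and adherence in newly diagnosed TB patients".

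The Inclusion criteria begin consistently with this: "Newly bacteriological confirmed TB cases (less than a month since diagnosis"). The next sentence restates the restriction as a one-month cap on treatment and says it "does not refer to patients whose most recent treatment outcome was a failure and assigned to a new treatment regimen".

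The Exclusion criteria cover critical illness, disability that prevents participation, pregnancy and private-clinic care. Previous treatment is not among them.

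Phases of pharmacist counselling places the first face-to-face interview "within two weeks of initiating of anti-tuberculosis treatment", after baseline data have been recorded.

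**The concern.** A patient whose most recent treatment ended in failure has already had a course of TB treatment with a recorded outcome. That patient is not a new case, and the present illness is not a new diagnosis in the sense of the objective. The eligibility text therefore appears to admit people outside the population that the trial says it studies.

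What is at stake is mainly whom the result describes. Failure is one of the unsuccessful categories of the primary treatment outcome, so an earlier failure is a plausible prognostic factor. If enough such patients enter, the pooled odds ratio refers to a mixed population that the objective does not name.

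The entry limit raises a second, smaller problem. Sites need to know which date starts the month, and they need to be able to deliver the first interview on schedule to everyone they enrol in the intervention arm.

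**Working it through.** The main point is a comparison of texts. The plan gives no figure to reproduce.

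**1. Population against eligibility**

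| Section | Who is covered |
|---|---|
| Trial Design; Intervention Group | New TB patients |
| Primary Objective | Newly diagnosed TB patients |
| Inclusion criteria, main clause | Newly confirmed, less than a month since diagnosis |
| Inclusion criteria, exemption | Restriction waived after a failed treatment, if on a new regimen |
| Exclusion criteria | No bar on previous treatment |

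The exemption can be read in two ways.

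- *Broad:* it admits previously failed patients. This contradicts the first two rows.
- *Narrow:* it waives only the time limit, and the patient must still be new. A patient whose last treatment failed cannot be new, so the sentence would then apply to nobody.

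The sentence needs correcting on either reading.

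**2. The two clocks and the interview window**

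- The limit is first counted from diagnosis, then as time on treatment. The two differ whenever treatment starts after the day of diagnosis.
- The first interview is due within 2 weeks (14 days) of starting treatment. Weeks 3-4 of treatment are days 15 to 28.
- A patient on days 15 to 28 of treatment is within the one-month treatment cap. If treatment began on the day of diagnosis, the same patient is also less than a month from diagnosis.
- That patient is eligible, but the 14-day window has closed. The interview follows baseline data, so it cannot have been held before entry.

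**3. Possible size (assumptions, not document figures)**

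Let *p* be the share of prior failures and *d* the effect in new patients. If prior failures gain nothing, the pooled effect is (1 − *p*)·*d* + *p*·0 = (1 − *p*)·*d*. With variance held fixed, the sample size for the same power grows by 1/(1 − *p*)².

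| Assumed share *p* | Pooled effect | Sample-size factor |
|---|---|---|
| 2% | 0.98 *d* | 1/0.98² = 1.04 |
| 5% | 0.95 *d* | 1/0.95² = 1.11 |
| 10% | 0.90 *d* | 1/0.90² = 1.23 |

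If the effect is the same in both groups, the pooled effect is (1 − *p*)·*d* + *p*·*d* = *d*, and there is no dilution. The article gives no share, success rate or effect for prior failures, so it cannot place the trial within this range.

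**The case against.** The strongest reply is that admission of these patients is only inferred. The exemption describes the waived restriction as a treatment-duration cap, and the requirement of new confirmation, together with the word new elsewhere, may still control entry. This shows that the intention is unclear. It does not rescue the sentence, which would then have no one to apply to.

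Second, randomisation is expected to balance prior failures between the arms. This stands: the point concerns the target population and possible dilution, and bias in the between-arm comparison is not implied.

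Third, stratification, covariates and subgroups are commonly left to a statistical analysis plan or full protocol, and neither is shown. This also stands. The absence of a stated analysis by treatment history is not part of the finding. An analysis plan could not settle whom the trial is about, however, because the objective and eligibility belong to the protocol.

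Fourth, the interview conflict arises directly only on the treatment clock, since time from diagnosis does not show that treatment has begun. That is right as far as it goes, but the protocol uses the treatment clock itself, and the conflict appears on both clocks when treatment starts promptly.

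A reader might also infer that previously failed patients would still be on treatment at six months and so be scored as unsuccessful. The document does not support this. Treatment Outcomes refers to outcomes unknown after the course is completed, which does not describe someone still in treatment. Table-I lists an unevaluated category without defining it, and the length of these patients' regimen is not given.

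**Conclusion.** The contradiction is real and can be shown from the text alone. The exemption either admits previously treated patients into a trial of new patients or has no effect. The one-month limit is stated on two clocks and permits entry after the first-interview window has closed.

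The consequence is moderate. The population to which the result applies is blurred, but the randomised comparison remains valid. The numerical effect cannot be computed from the document. It ranges from no dilution, if prior failures benefit equally, to a 10% loss of effect and a sample-size factor of about 1.23, if they make up 10% of patients and gain nothing. Those shares and the zero effect are assumptions. A stronger conclusion, that the trial could not answer its question for new patients, would need a large share of prior failures, and nothing in the article indicates one.

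**What to change.** Reconcile the Inclusion criteria with Trial Design, Primary Objective and Intervention Group in one of two ways.

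1. Delete the exemption, so that eligibility matches the stated objective. This costs one sentence and a slightly smaller eligible pool.
2. Restate the population and objective as new and previously failed TB, and adjust the logistic model for treatment history. This costs one covariate, a record of treatment history at baseline and a broader claim.

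The study period starts in August 2019 and the article already cites 2019 burden figures, so enrolment may have begun. If it has, deleting the sentence would not remove patients already randomised. In that case use the second option and also report the result in new patients.

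Under either option, state the entry limit on a single clock, with its starting date named, and make it consistent with the first-interview window in Phases of pharmacist counselling. The investigators must decide how those two passages are brought together. The cost is a wording change and a note to sites.

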### Exclusion criteria:

Who are critically ill,Have a physical disability that prevents full participation in the study such as vision, hearing, physically challenged, unable to answer questionsPregnant females,Patients receiving treatment from private clinics (who are not registered in the government TB sectors, and they seek care from private health care facilities).

### Intervention Group:

The study will be conducted among all eligible new TB patients who are registered and receiving their treatment from the TB Control Center of PIMS and DBTC. In the intervention group, the participant’s pharmacist will provide pharmaceutical care education at each follow-up visit and SMS reminders will be sent to patients in local and in national language. The messages will be aimed ‘to take their prescribed anti-TB drugs daily and record the behaviour change during the therapy.

### Phases of pharmacist counselling:

After documentation of base-line data, patient care interventions will be implemented. Pharmaceutical care will be provided face to face during monthly follow ups visits to health care center. Interventions will be divided into non-pharmacological and pharmacological. Non-pharmacological interventions included guidance on the proper use of drugs and their risks and pharmacological interventions included suspension, addition, or change in medication. If pharmacological interventions seem to be necessary, a collaborative decision will be made by the pharmacist, physician, and patient. The pharmacist will talk over the patient-related barriers to adherence, incomplete information related to medication and disease, and other drug-related problems.The pharmaceutical care and face-to-face counselling to the TB patients will be provided during the first interview, within two weeks of initiating of anti-tuberculosis treatment. The second interview will be conducted within two months. The third interview will be at the six month of the treatment and the final data will be collected before the final sputum test.

### Blinding:

Due to this study’s nature, it will not be possible that the patients and will remain entirely blinded to the principal investigator because they will receive SMS reminders and pharmaceutical care. Data collector and analysis team or other study-related pharmacists carrying out study outcome measurements such as treatment outcomes, adherence, quality of life and satisfaction questionnaire, will remain fully blinded to the allocation of the control and intervention group Table-II.

**Table-II T2:** Overall binding scheme

Stakeholders	Allocation scheme	Pharmacist Intervention	SMS Sender	Outcome assessment	Data analysis
Trial observer	Aware	Aware	Aware	Aware	Aware
Participants	Aware	Aware	Aware	Not aware	Not aware
Pharmacists	Aware	Aware	Aware	Not aware	Not aware
Pulmonologists	Aware	Aware	Aware	Not aware	Not aware
Data collectors	Not aware	Not aware	Not aware	Not aware	Not aware
Data analysis	Not aware	Not aware	Not aware	Not aware	Aware

### Sample size:

Considering the drop out in the study up to 10%, the intended sample size is 413 subjects per group is needed. Over a six month period between the groups, with a two-tailed α of 0.05 and (1-β) of 0.80 using the formula the total intended sample size is 426 patients for both groups.

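### The sample size section gives two intended sizes that cannot both be right: 413 per group (826 in all) and 426 in all (213 per group)

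*Protocol article*

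**What the plan says.** The Sample size section of the protocol article has two sentences. The first allows for up to 10% dropout and states that "the intended sample size is 413 subjects per group is needed". The second refers to a six-month comparison, gives the error rates as "with a two-tailed α of 0.05 and (1-β) of 0.80", and ends "using the formula the total intended sample size is 426 patients for both groups". Both figures are called the intended size.

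The Trial Design section fixes the allocation: "The study will be randomized into two parallel groups (ratio 1:1". No other part of the text shown repeats either number or says which one governs. The study flow diagram (Fig. 1) is not reproduced in the text at hand, so it cannot be used either way.

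**The concern.** With two equal groups, a per-group size and a total must differ by a factor of two. Here the stated total is only 13 larger than the stated size of one group. The alpha and power are given once, yet they sit beside two designs of which one is almost twice the other.

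The sample size is the recruitment target and carries the power claim. With two targets in print, a reader of the results cannot tell whether the trial reached its planned size, and cannot check the 80% power. If the larger figure was what the calculation required and the smaller was recruited, the trial would have had roughly an even chance of detecting the effect it was designed for.

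**Working it through.** **Inputs, all from the protocol article**
- Two-sided alpha 0.05 and power 0.80 (Sample size), so z₀.₉₇₅ = 1.960, z₀.₈₀ = 0.842, sum 2.802.
- Two groups, 1:1 (Trial Design).
- Dropout up to 10% (Sample size).
- Stated sizes: 413 per group; 426 for both groups (Sample size).
- No effect size, event rate or SD is printed, so neither size can be rebuilt from first principles. The checks below do not need one.

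**Step 1: put both figures on the same footing**
- 2 × 413 = 826, not 426.
- 426 / 2 = 213, not 413.
- 413 / 213 = 1.94.

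**Step 2: does dropout link them?**
- 213 per group is the evaluable number: 213 / 0.9 = 237, or 213 × 1.1 = 235 after rounding up. Neither is 413.
- 413 per group already includes dropout: 413 × 0.9 = 372 evaluable, not 213.
- 413 is really a total before dropout: 413 / 0.9 = 459, or 413 × 1.1 = 455 after rounding up. Neither is 426.
- 426 is a total after inflation: 426 × 0.9 = 383, or 426 / 1.1 = 387. Neither is 413.

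**Step 3: does another alpha or power link them?** For a fixed effect, n is proportional to (z_alpha + z_power)².
- One-sided alpha 0.05 instead of two-sided multiplies n by 0.79.
- 90% power instead of 80% multiplies n by 1.34.
- The factor needed is 1.94 (or its inverse, 0.52). Neither change gives it.

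**Step 4: power at one size if 80% holds at the other.** By the normal approximation, for the same effect,

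power = Φ(2.802 × √(n_actual / n_design) − 1.960)

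| 80% power holds at (per group) | Size used (per group) | Calculation | Power |
|---|---|---|---|
| 413 | 213 | Φ(2.802 × √0.516 − 1.960) = Φ(0.052) | 52% |
| 213 | 413 | Φ(2.802 × √1.939 − 1.960) = Φ(1.941) | 97% |
| 371.7 (413 less 10%) | 213 | Φ(2.802 × √0.573 − 1.960) = Φ(0.161) | 56% |
| 213 | 371.7 (413 less 10%) | Φ(2.802 × √1.745 − 1.960) = Φ(1.741) | 96% |

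Taking 10% off both sizes leaves the ratio, and so the first two rows, unchanged. The last two rows apply if only the 413 already includes dropout.

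**Step 5: what each size can detect.** The standardised difference detectable with 80% power is 2.802 × √(2/n): 0.195 at 413 per group and 0.272 at 213 per group.

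**The case against.** The strongest reply is that this is a misprint and not two designs. The implied per-group size, 213, differs from 413 in one digit, and the sentence giving 426 also carries the alpha, the power and the reference to a formula. On that reading 426 is the real target and one figure needs correcting. This is plausible but not established. The same argument runs the other way, because 826 differs from 426 in one digit. The 413 could also be a total mislabelled as per group. Under any of these readings at least one printed number is wrong.

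Three stronger readings are tempting, and the document does not support them.

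- *A reader might infer that the missing effect size is itself a fault.* The source is a condensed journal article that refers to a formula without showing it, and the full protocol may set it out. The omission matters here only because it stops a reader from working out which number is the calculated one.
- *A reader might infer that a null result would be uninterpretable.* The section on statistical analysis and ethics approval plans an odds ratio with a 95% CI for cure rates. That interval can be read whatever the planned size was. What is lost is the check on the power claim and on whether the target was met.
- *A reader might infer that recruitment will stop at half the needed number or run to twice it.* That supposes the article governs recruitment. The full protocol may give a single target.

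It is also fair to say that the article attaches the dropout allowance only to the 413. That is why the power figures are given on both dropout readings; the conclusion does not depend on the choice.

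**Conclusion.** The section is wrong as written. It gives two intended sizes that differ by a factor of 1.94 at the stated 1:1 allocation, and neither the dropout allowance nor the other alpha and power values tried reconcile them. For one assumed effect, 80% power cannot hold at both. The cost of the ambiguity is power of about 52% at the smaller size if the larger was required, or about 97% at the larger if the smaller was required (about 56% and 96% if only the 413 includes dropout).

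These power figures rest on the normal approximation, equal groups and the same effect at both sizes. They need no assumption about event rates. The document does not allow a conclusion on which size is right, on whether either truly gives 80% power, or on which of the primary outcomes drove the calculation.

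**What to change.** Go back to the trial's sample size calculation and state one size, per group and in total, saying whether it is before or after the 10% dropout allowance.

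- If 426 in total is operative, correct the per-group figure to match (213). If the calculation in fact required 413 per group, also restate the power or the detectable difference that 426 patients deliver.
- If 413 per group is operative, correct the total to 826.

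The restated power or difference should use the inputs of the trial's own calculation, not values chosen afterwards to suit the number.

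The cost is a correction to two sentences and, in one case, a recalculated power. If 426 is the real recruitment target, no extra patients are needed; the downside is that the stated power may become less favourable. If 413 proves to be a misprint for 213, a single figure changes, and the design and analysis stay as they are.
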